**Figure 2 figure2:**
[figure not shown]
Map of EMERALD (Enabling Mobilization, Empowerment, Risk Reduction, and Lasting Dignity) intervention and control areas. Red star=SPARC (Sex Workers Promoting Action, Risk Reduction, and Community Mobilization) center, blue=water, pink=intervention area, and green=control area.

SPARC’s day-to-day operations are bolstered by key collaborations with community providers who offer services at SPARC, enabling these organizations to reach a population they otherwise do not easily access. The Baltimore City Health Department funds 2 nurse practitioners and a medical assistant to run a weekly reproductive health clinic (eg, long-acting reversible contraceptives, Papanicolaou testing, and intrauterine devices) and a twice-weekly sexual health clinic (eg, pre-exposure prophylaxis, HIV and Hepatitis C testing and treatment referrals, and STI testing and treatment). The Behavioral Health Leadership Initiative funds 2 providers to staff a weekly low-threshold medication-assisted treatment clinic at SPARC. Biweekly law clinics are offered through the Legal Aid of Maryland and the Maryland Volunteer Lawyers Network.

SPARC’s reach is expanded through an intensive mobile outreach program, which brings many tangible harm reduction tools and microcounseling to women while they are working and living on the street. The outreach program is deployed throughout south and southwest Baltimore at night and during the day between 3 and 4 times a week, serving 15 to 40 people per shift. Outreach staff work in teams to provide relevant harm reduction education and supplies from the window of the outreach vehicle, through drop-off supply bags, and during community events.

All SPARC and outreach staff receive extensive training as a part of onboarding and continuing education. Training sessions are conducted by the study staff as well as external experts and cover topics such as trauma-informed care, harm reduction principles and practice, interpersonal and systemic violence, safer drug use (eg, safer injection), naloxone administration, gender and sexual identity, and de-escalation and staff safety practices. Understanding that trauma often serves as a direct barrier to care, much of the continuing education at SPARC centers around trauma-informed care and supporting the complex needs of vulnerable individuals.

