### The EMERALD Study

#### Study Design

The primary component of the EMERALD study, which evaluates the SPARC center and associated outreach, is a prospective 2-group comparative nonrandomized trial. Participants were recruited into the control and intervention arms. The intervention area is the south and southwest portion of Baltimore City because of high concentrations of street-based FSWs and a dearth of tailored FSW services, indicated by pink shading (Figure 2). The control group participants were recruited primarily from the southeast and northwest Baltimore. The SPARC center is located within the intervention area, and outreach is conducted in areas with potential sex work activity throughout the intervention area.

The study diagram (Figure 3) illustrates participant progress through the study stages, sample size, and follow-up schedule. Participants completed a survey, HIV testing, and STI testing for chlamydia and gonorrhea during study visits at baseline and at 6, 12, and 18 months. In-depth interviews began at the conclusion of the EMERALD cohort and are currently being conducted with intervention area participants, SPARC staff, and outreach workers. In addition, 100 cross-sectional surveys are being collected in the intervention area to assess program reach in the community beyond the EMERALD cohort.

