	**Empowerment [54]**	
		I have little control over the things that happen to me; 5-point Likert scale (totally disagree to total agree)
		There is little I can do to change many of the important things in my life; 5-point Likert scale (totally disagree to total agree)

^a^N/A: not applicable.

On completion of the survey, participants were asked to self-collect vaginal swabs with Aptima vaginal swabs (Hologic Inc) using the private RV bathroom. The samples were sent to the Baltimore City Health Department lab, which conducted nucleic acid amplification testing for gonorrhea and chlamydia. Once samples were collected, the participants received the results of their HIV test and posttest counseling. A 2-week appointment was scheduled to receive the STI test results.

Participants were given a US $70 prepaid Visa debit card as compensation for their time and offered relevant referrals to health and social services. Participants recruited from the intervention area were encouraged to visit SPARC and offered hygiene products such as sanitizer wipes and lip balm with SPARC branding, including the address and phone number of the center. Control area FSWs were offered similar EMERALD-branded items and provided neighborhood-specific referrals if requested but were not encouraged to visit SPARC.

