For the primary biological endpoint of HIV and STI incidence, we will initially estimate cumulative incidence rates in both the intervention and comparison participants as a binary outcome and construct confidence intervals, accounting for the correlation structure because of nesting in geographic recruitment areas. The intervention’s effect will be assessed using an unadjusted random effect logistic model, with the intervention indicator as the only explanatory variable. The model will be expanded to include baseline covariates, such as demographic characteristics, history of sex work, and baseline risk behaviors (ie, condom use). A more detailed analysis will employ person-time methods with Poisson regression models to allow for time-updated covariates measured over time. Those lost to follow-up will contribute time-at-risk until the time of their last visit.

Finally, to evaluate the reach of the intervention, we will estimate SPARC involvement of FSWs in the independent cross-sectional survey at the 18-month follow-up period. We will also compare this sample with the FSW cohort at 18 months to assess their comparability or differences regarding demographic and risk profiles using logistic regression with group membership as the outcome variable.

To address aim 2, we will first describe changes over time in various sociostructural (ie, social cohesion and stigma) and structural vulnerability (eg, housing stability) indicators. We will then contrast these trends between the intervention and comparison groups. Social cohesion, social participation, and collective action will be analyzed as aggregate measures, the form of which will be determined by exploratory analysis. Specific models for formal statistical comparisons will be developed based on exploratory analysis, identifying both the distributional properties of the indicators and the shape of changes over time. To assess the association of these changes with the study’s primary endpoints, we will develop random effects logistic models, where the changes in structural indicators at each visit compared with baseline will be the main explanatory factors, in addition to the intervention indicator. The random effects will reflect the nesting of observations within the recruitment area and person over time.

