### Cohort Participant Characteristics

The final sample of the cohort (n=385) had a mean age of 37 years (SD 9.3 years), 56.6% (218/385) of participants were White, 70.9% (273/385) had attained less than a college education, and approximately two thirds of the sample (257/385, 66.8%) had a recent history of homelessness (Table 2). There were significant differences in racial categories between the intervention and control areas (*P*=.04). Women reported an average of 13 years (SD 9.5 years) in sex work. The prevalence of current substance use was high: 57.9% (223/385) injected any drug, 80.3% used heroin via any method, and 86.8% (334/385) used powdered or crack cocaine in the past 6 months. Almost half of the sample (174/385, 45.2%) reported a recent condomless sex with clients. HIV prevalence in the full sample was 5.2% (20/385), although only 3 women received new HIV diagnoses from study-related testing. Baseline gonorrhea and chlamydia prevalence were high at 15.8% (59/373) and 18.2% (68/374), respectively. There were no significant differences between the control and intervention groups in the key study outcomes at baseline.

**Table 2 table2:** Baseline characteristics of a sample of female sex workers in Baltimore, Maryland, recruited to the EMERALD (Enabling Mobilization, Empowerment, Risk Reduction, and Lasting Dignity) study (n=385).

Variables						Total (n=385)			Intervention (n=224)			Control (n=161)			*P* value	

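### The gonorrhoea and chlamydia endpoint is called incidence but is seen only on swabs 6 months apart, while the intervention tests and treats these infections between swabs, so positivity can fall without lower acquisition

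*Protocol article*

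**What the plan says.** All places are in the protocol article.

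- **Endpoint (Statistical Analysis).** HIV and STI incidence is the primary biological endpoint: "we will initially estimate cumulative incidence rates in both the intervention and comparison participants as a binary outcome". The effect is first assessed in a random-effects logistic model "with the intervention indicator as the only explanatory variable". Then: "The model will be expanded to include baseline covariates, such as demographic characteristics, history of sex work, and baseline risk behaviors (ie, condom use"). A Poisson person-time analysis follows.
- **Ascertainment (Study Design).** Participants had "STI testing for chlamydia and gonorrhea during study visits at baseline and at 6, 12, and 18 months". No other source of STI outcomes is described.
- **Intervention content (Intervention: The SPARC Center and Outreach Program).** SPARC hosts "a twice-weekly sexual health clinic (eg, pre-exposure prophylaxis, HIV and Hepatitis C testing and treatment referrals, and STI testing and treatment").
- **Access by arm (Cohort Recruitment, after Table 1).** "Participants recruited from the intervention area were encouraged to visit SPARC". Controls were not encouraged to attend, but nothing bars them. A results appointment 2 weeks after testing, and relevant referrals, are described without distinction by arm.
- **Linkage (Intervention section).** SPARC and study records are to be linked to find how often participants used the center. Diagnoses are not mentioned.
- **Baseline (Cohort Participant Characteristics).** "Baseline gonorrhea and chlamydia prevalence were high at 15.8% (59/373) and 18.2% (68/374"). Table 2 shows both infections less often in the intervention arm.

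**The concern.** A swab shows whether a woman is infected on that day. Over a 6-month gap, the chance of a positive swab depends on how often infections are acquired and on how long they last. Testing and treatment at SPARC shortens infections, and it is promoted in one arm. An infection acquired and cured between two study visits leaves no trace in the outcome data, and this should happen more often among intervention women. The same acquisition in both arms can then give fewer positive swabs in the intervention arm.

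The stated hypothesis is a reduction in incidence. A favourable result on this endpoint could reflect fewer infections, shorter infections or both, and the swabs alone cannot separate them. The Poisson analysis uses the same swab-detected events, so it inherits the problem. A participant who misses a visit may still attend the next, which can lengthen the unseen gap to about 12 months.

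Baseline infection is a lesser matter. It is numerically more common in controls, and neither the first model nor the listed expansion covariates include it.

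**Working it through.** **1. Baseline figures.** Table 2 prints counts and percentages by arm. Denominators back-solved from them, with Pearson chi-square tests:

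- Gonorrhoea: 30/219 = 13.7% vs 29/156 = 18.6%; P = .20, as printed; ratio 0.74.
- Chlamydia: 33/219 (or 33/218) = 15.1% vs 35/158 = 22.2%; P = .08, as printed; ratio 0.68.

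**2. Acquisition rate, set equal in both arms.** The Background gives 12-month incidence in the earlier Baltimore cohort of 13.7% (chlamydia) and 18.2% (gonorrhoea). As rates:

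- chlamydia: −ln(1 − 0.137) = 0.147 per year
- gonorrhoea: −ln(1 − 0.182) = 0.201 per year

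**3. Between-visit treatment alone.** Let λ be acquisition and μ clearance, per year. For a woman uninfected at one visit, the chance of a positive swab 0.5 years later is

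p = λ/(λ + μ) × (1 − exp(−0.5(λ + μ))),

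and the chance of at least one positive in three visits is 1 − (1 − p)³.

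Assumptions, not in the documents: background clearance 0.5 per year in both arms; extra clearance s in the intervention arm; everyone uninfected after the baseline visit.

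Chlamydia, worked:
- Control, μ = 0.5: p = 0.063, so 1 − 0.937³ = 0.177.
- Intervention, s = 1.0, μ = 1.5: p = 0.050, so 1 − 0.950³ = 0.143.
- Apparent risk ratio 0.143/0.177 = 0.81, with the true ratio 1.00.

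| s per year | Chlamydia RR | Gonorrhoea RR |
|---|---|---|
| 0.25 | 0.95 | 0.95 |
| 0.5 | 0.90 | 0.90 |
| 1.0 | 0.81 | 0.81 |

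The assumed background clearance matters little: between 0.25 and 2 per year, the ratio at s = 1.0 stays at 0.80 to 0.83.

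At the planning sizes for this outcome (170 and 120), a two-sided 5% test should favour the intervention by chance 2.5% of the time. Across s = 0.25 to 1.0 this becomes 4% to 12% for chlamydia and 4% to 15% for gonorrhoea.

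**4. Baseline infection alone.** Same model with s = 0 in both arms. A share c of baseline infections is cleared after the study result; the rest start follow-up infected, and a positive swab from them is counted. With c = 100%, 80% and 50% (assumed):

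- Chlamydia RR: 1.00, 0.96, 0.91.
- Gonorrhoea RR: 1.00, 0.98, 0.95.

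A cruder check sets counted risk = 1 − (1 − 18-month incidence) × (1 − baseline prevalence × persistence). The 18-month incidences are 1 − 0.863^1.5 = 0.198 and 1 − 0.818^1.5 = 0.260. With 20% to 60% persistence (assumed), the null odds ratios are 0.94 to 0.85 for chlamydia and 0.97 to 0.91 for gonorrhoea. At zero persistence there is no bias.

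**The case against.** **Treatment is part of the intervention.** STI testing and treatment is a stated component, so fewer infected women at each visit is partly the intended benefit. That stands, and lower positivity is worth reporting. It is still not the same as lower acquisition, which is what the word incidence claims.

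**A case definition may exist elsewhere.** A reader might infer that persisting baseline infections are counted as incident. The article does not say so: it gives no incident-case rule, and it states that full analysis details are available on request. The baseline point is therefore conditional. The between-visit point is not, because no case definition can recover infections that study swabs never saw.

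**Controls also have access to care.** A reader might infer that treatment exists in one arm only. The documents support less: controls were not encouraged to visit SPARC but were not barred, and they too had study testing, results and referrals. What matters is the between-arm difference in clearance, which the documents do not quantify.

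**The baseline differences are not significant.** True (P = .20 and .08), and the article reports no significant baseline difference in key outcomes. Non-significance does not remove a numerical imbalance from an unadjusted comparison, but the effect on its own is small.

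**Conclusion.** The point holds as a limit on what the gonorrhoea and chlamydia endpoint can show. Swab positivity at 6-monthly visits mixes acquisition with duration, and the intervention acts on duration. With no difference in acquisition, the apparent risk ratio is about 0.95 to 0.81 for an assumed extra clearance of 0.25 to 1.0 per year. These figures illustrate the mechanism and do not estimate the bias in this trial, because clinic uptake and infection duration are not given.

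The baseline imbalance is secondary: null risk ratio about 0.91 to 1.00, and only if some baseline infections persist and are counted.

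It would go too far to say that the result is bound to favour the intervention or that the whole biological endpoint is compromised. The HIV component is not affected by this mechanism.

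**What to change.** 1. **Name and claim.** Report the STI endpoint as infection detected at 6-monthly study visits, and state that a difference between arms is not to be read as reduced acquisition alone. This costs only wording. It is the main remedy, because the analysis cannot recover unseen infections.

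2. **Baseline infection.** For each organism, count a follow-up positive as incident only after a prior negative swab or documented treatment, with treatment records drawn from the same sources in both arms. At the least, adjust for baseline infection status. Report the alternative as a sensitivity analysis. Under the prior-negative rule about 16% (gonorrhoea) to 18% (chlamydia) of women leave the first interval's risk set, a small loss of precision. That rule also drops women treated and reinfected by month 6, never admits a woman positive at every visit, and removes proportionally more controls, which is why the sensitivity analysis is needed.

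3. **SPARC diagnoses.** Count these only as an exploratory bound, and only if the consented, linked records prove to contain diagnoses; the article describes the linkage for visit frequency alone. Such a count adds events mainly to the intervention arm and ignores diagnoses that controls receive elsewhere, so it bounds the effect in one direction only.

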#### Cohort Study Target Population and Sample

Cohort participants were FSWs aged ≥18 years who live in Baltimore City; self-reported that they had traded sex for money, goods, or drugs 3 or more times in the past 3 months; and were not currently enrolled in our previous cohort study, the SAPPHIRE study [40]. Although transgender female sex workers (TFSWs) who reported being assigned male at birth were encouraged to visit the SPARC center and engage with peer outreach workers, they were excluded from the EMERALD study cohort because of a lack of comparable recruitment locations between the intervention and control areas.

Participants were assigned to a study arm based on the geographic location in which they were recruited. The initial target sample size was 350 women based on power calculations to observe a change in the intervention compared with the control group over the 3 follow-up visits. The assumptions used for the calculation were (1) n=200 in the intervention group and n=150 in the comparison group, (2) lost-to-follow-up (LTFU) rate of 10% to 20% in the intervention (effective n=160-180) and LTFU of 20% to 25% in the comparison group (effective n of 120-112), (3) intraperson correlation (Rho)=0.2-0.4, (4) varying levels of baseline risk behavior rate, and (5) a 2-sided α=.05. Thus, assuming effective sample sizes of n=160 in the intervention and n=112 in the comparison groups, the power is 83% to detect an odds ratio of 0.50, assuming a 20% prevalence rate of a risk behavior (eg, drug use) in the control group and an intraperson correlation of Rho=0.2. For the cumulative incidence outcome, with an average N contributing to the analysis of 170 in the intervention and 120 in the control groups, and assuming annual incidence rate of 6%, the power is 80% to detect a rate ratio of 0.28.

The enrollment target was increased to 450 midway through data collection after power calculations were reassessed based on actual retention rates within the sample, which were closer to 65%. The LTFU rate was higher than anticipated based on previous studies [41], likely because of high incarceration rates, the mobility of the population, and the length of time between study visits (6 months). Although we aimed for a sample of 450 participants, recruitment was stopped at 385 because of reaching saturation in the recruitment areas and repeatedly encountering participants attempting to reenroll in the study.

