#### Cohort Retention Methods

Follow-up visits for EMERALD occurred at 6, 12, and 18 months after the initial baseline interview. Participants received US $40 prepaid Visa debit cards for completing each follow-up visit. Participants were eligible to complete each follow-up visit 1 month before their actual interview date until 1 month after, for a total eligibility window of 2 months. Those who failed to complete an interview within the allotted eligibility window were considered lost to follow-up. Participants who missed a visit could still complete their next scheduled visit and were not withdrawn from the study.

Retention protocols were modeled after strategies used in SAPPHIRE [50] and are more fully described in a study by Silberzahn et al [41]. Briefly, retention strategies consisted of the aforementioned locator forms (eg, phone numbers, addresses, and social media accounts); promotional materials (eg, hand sanitizer, wipes, lip balm, and silicon bracelets) branded with the study logo and phone number; monitoring public information databases to determine if participants were incarcerated, had moved, or were deceased; and outreach in the form of phone calls, social media messaging, home visits, and repeated visits to recruitment areas in both the study RV and a study sedan, which was used for follow-up. The study team also relied on tracking teams of 2 study staff who were assigned participants to focus on with 1 month of eligibility remaining.

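### The lead test for HIV/STI incidence ignores how many follow-up tests each woman completed, and the person-time model that largely accounts for this is ranked behind it

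*Protocol article*

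**What the plan says.** The Statistical Analysis section of the protocol article treats HIV and STI incidence as one binary value per woman: "we will initially estimate cumulative incidence rates in both the intervention and comparison participants as a binary outcome and construct confidence intervals". The intervention's "effect will be assessed using an unadjusted random effect logistic model, with the intervention indicator as the only explanatory variable". Two further steps follow. First, "The model will be expanded to include baseline covariates", with demographics, sex work history and baseline risk behaviors as examples. Second, "A more detailed analysis will employ person-time methods with Poisson regression models to allow for time-updated covariates measured over time", where women lost to follow-up contribute time up to their last visit. The only correlation named for this endpoint is nesting in recruitment areas.

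Tests are scheduled at 6, 12 and 18 months. Under Cohort Retention Methods, "Participants who missed a visit could still complete their next scheduled visit and were not withdrawn from the study". Under Cohort Study Target Population and Sample, the sizing assumed a loss to follow-up "rate of 10% to 20% in the intervention (effective n=160-180) and LTFU of 20% to 25% in the comparison group". The target was later raised because of "actual retention rates within the sample, which were closer to 65" per cent. That figure is pooled over the arms. The Limitations section adds that 27 participants could not be tested for HIV and STIs because of COVID-19, also without a split by arm.

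**The concern.** Chlamydia and gonorrhea are counted only at a completed swab. At the same true risk, a woman with three swabs has more chances to be counted positive than a woman with one. An arm-only model on one yes/no value per woman therefore mixes acquisition with amount of testing, and adjusting for baseline covariates does not separate the two.

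If the intervention arm is better retained, as most of the original sizing range implies, the odds ratio is pushed above its true value: a benefit shrinks, or a null effect looks like harm. If the control arm is better retained, the error favors the intervention. A gap in either direction cannot be excluded. One route to a gap is in the design: women at the SPARC center could use its phone to schedule study visits, and only intervention-area participants were encouraged to go there.

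**Working it through.** **The plan's own figure.** The article states 80% power for a rate ratio of 0.28, with 170 vs 120 women and 6% annual incidence. A two-proportion formula gives 67% over 18 months (9% vs 2.5%) and 79.6% only over 24 months (12% vs 3.4%). That is a separate matter; nothing below depends on it.

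**Inputs**
- Risk per 6 months, h. The earlier cohort quoted in the Introduction had 13.7% chlamydia and 18.2% gonorrhea over 12 months. Assuming independence, h = 1 − √(0.863 × 0.818) = 0.160. The plan's 6% per year, h = 1 − exp(−0.03) = 0.030, is used as the low case.
- Retention r, intervention/control. 90/75% (extremes of the sizing ranges), 85/77.5% (midpoints), and 70/58% (my assumption, chosen to average (224 × 0.70 + 161 × 0.58)/385 = 65%).
- Arms of 224 and 161, equal h in both arms, missingness unrelated to infection, area effects ignored, denominator = women with at least one follow-up test.

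**Probability of being counted positive**
- *Independent missed visits, infection clears unseen:* P = [1 − (1 − rh)³] / [1 − (1 − r)³]. At 90/75: 0.3724/0.999 = 0.373 vs 0.3182/0.984 = 0.323, odds ratio 1.24 (1.25 when simulated).
- *Permanent dropout, r reached at month 18:* with q = r^(1/3), P = {q(1 − q)h + q²(1 − q)[1 − (1 − h)²] + q³[1 − (1 − h)³]}/q. At 90/75: 0.395 vs 0.375, odds ratio 1.09.
- *Independent missed visits, infection still detectable later:* P = Σ r(1 − r)^(3−k)[1 − (1 − h)^k] / [1 − (1 − r)³], k = 1 to 3. At 90/75: 0.3945 vs 0.3736, odds ratio 1.09. If it stays detectable only to the next scheduled visit, a woman tested only at month 18 reveals two intervals instead of three: 0.3935 vs 0.3683, odds ratio 1.11.

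**Results with no true effect, h = 0.160** (rejection from simulated two-sided 5% Wald tests)

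| Mechanism | OR 90/75 | OR 85/77.5 | OR 70/58 | Rejection | Rate ratio, time to last visit |
|---|---|---|---|---|---|
| Permanent dropout | 1.09 | 1.04 | 1.08 | 5–6% | 1.00 |
| Missed visits, infection persists | 1.09–1.11 | 1.05–1.06 | 1.08–1.10 | 5–8% | 1.01–1.03 |
| Missed visits, unseen clearance | 1.24–1.25 | 1.12 | 1.18 | 17%, 8%, 10% | 1.12, 1.06, 1.09 |

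At 6% per year the null odds ratio is at most 1.19 and rejection stays at 4% to 6%. With equal retention it is 1.00 throughout.

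**With a real effect, extreme case only.** Take 10% vs 16% per 6 months, 90/75 and unseen clearance. The true 18-month odds ratio is (0.271/0.729)/(0.407/0.593) = 0.54. The binary model gives 0.68 with 39% power, against 75% for an interval-level model on the same data.

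**Level of incidence.** At equal 65% retention with unseen clearance, crude cumulative incidence is [1 − (1 − 0.65 × 0.160)³]/[1 − 0.35³] = 29%, against a true 1 − 0.84³ = 41%.

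**How time at risk is counted.** Under unseen clearance, counting only tested intervals gives a rate ratio of 1.00. If infections persist, that count must allow for interval length. At 90/75 the rates per tested interval are 0.3941/2.319 = 0.170 vs 0.3678/1.972 = 0.186, a ratio of 0.91. Here the numerators are events per woman, and the denominators are r × (1 + probability of not being positive by visit 1 + the same by visit 2).

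**The case against.** The strongest reply is that the plan anticipates unequal follow-up. The binary estimate is described as an initial step, and the same section plans Poisson regression with time at risk. That stands: a reader might infer that the plan has no answer to unequal observation, and the text does not support this. The Poisson model removes the bias under permanent dropout and nearly all of it if infections persist. What is left is that the effect is assessed first in the model without that protection, and that time credited up to the last visit leaves a rate ratio of about 1.06 to 1.12 under skipped visits with unseen clearance.

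Other limits also stand:
- The loss ranges by arm are original sizing assumptions, overtaken by pooled retention near 65%, and they meet at 20%, where between-arm bias is zero. Concluding that the result is biased against SPARC goes beyond the article.
- An odds ratio of 1.25 needs the widest gap, independent misses and every missed infection clearing. The article gives no clearance figure, and HIV, part of the endpoint, does not clear.
- A reader might also infer that the trial was powered on a different analysis, because the sizing names a rate ratio. This is not established. The article uses rate language for cumulative incidence too, and the stated power comes closest to a comparison of two proportions.
- Ever positive among tested women is the natural reading of a binary cumulative incidence, but the article does not spell it out, and full analysis details are held elsewhere.

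**Conclusion.** The point holds as one about which model leads and how time at risk is counted. As written, the lead test gives a biased odds ratio whenever completed testing differs by arm. Under the stated assumptions the bias is modest in the likelier mechanisms (null odds ratio about 1.04 to 1.11, rejection 5% to 8%). The extreme is 1.25 with 17% rejection, and at the plan's own 6% incidence the ceiling is about 1.19. Neither the actual gap nor its direction can be read from the article. With equal retention the arm comparison is not biased in this way, but missed tests still make crude cumulative incidence too low in both arms.

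**What to change.** In the Statistical Analysis section, make the effect test for HIV/STI incidence a rate-based model that accounts for observation: either the Poisson model already planned, or a discrete-time complementary log-log model over completed test intervals. Include a term for interval length and recruitment area as the clustering level. Leave out a woman-level random effect, which is weakly identified when each woman has at most one first event.

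For chlamydia and gonorrhea, count time at risk over tested intervals rather than simply to the last visit, and show the last-visit version as a sensitivity analysis. The first is exact under unseen clearance and the second nearly so under persistence, so the pair shows how much this unknown matters. In the complementary log-log model, estimate the coefficient of log interval length rather than fixing it: it is 0 under clearance and 1 under full persistence.

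Report cumulative incidence from that model or a life table, keep the one-value-per-woman logistic model as descriptive, and tabulate completed tests per woman by arm.

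The cost is a change of wording and modest programming on visit and test data already collected. The downside is a slightly less simple headline estimate.
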